## Abstract

**Background:**

Accurate and rapid diagnosis of early-onset neonatal sepsis (EOS) in preterm infants remains problematic due to a lack of specific symptoms and diagnostic tools. Following the Dutch EOS guidelines, over 80% of infants born < 32 weeks of gestation are empirically started on antibiotics directly after birth, while the actual incidence of EOS varies between 1 and 2%. Unnecessary antibiotic exposure leads to severe short and long-term complications. The biomarker presepsin, also known as soluble CD14 subtype, may be used to reduce antibiotic prescription in preterm infants after birth. The objective of this study is to investigate whether adding a presepsin-guided decision to the guideline safely reduces antibiotic exposure directly after birth in preterm infants. Secondly, the diagnostic accuracy of presepsin for EOS will be evaluated.

**Methods:**

The PRESAFE trial is a multicentre, randomized controlled trial (RCT), including a concurrent observational study. Presepsin levels are determined from umbilical cord blood or during the first regular blood draw in all infants born < 32 weeks gestation. Infants who qualify for empirical antibiotics according to the Dutch EOS guideline are categorized as moderate or high risk for EOS based on prespecified high-risk criteria. Infants not qualifying for empirical antibiotics are categorized as low risk. Preterm infants with a moderate risk for EOS are randomized 1:1 into an intervention arm and a comparator arm. In infants allocated to the intervention arm, empirical antibiotics will only be started above a prespecified presepsin level of ≥ 645 pg/ml. In the comparator arm, infants will be treated according to the standard of care following the Dutch EOS guideline, equivalent to starting empirical antibiotics. The co-primary outcomes of the RCT are the incidence of culture-proven EOS (non-inferiority) and unnecessary antibiotics administration (superiority). The required sample size for the RCT is 900 patients. Infants with a high- or low-risk of EOS are excluded from randomization but included in a concurrent observational study and treated according to the Dutch EOS guideline. The primary outcome of this part is the diagnostic accuracy of presepsin.

**Discussion:**

The findings of the RCT will provide evidence for safe and effective reduction of administration of antibiotics for suspected EOS in infants born < 32 weeks of gestation. The observational study will provide more insight in the diagnostic accuracy of all infants born < 32 weeks of gestation.

**Trial registration:**

ClinicalTrials.gov NCT06100614. First registered on October 25, 2023.

## Administrative information

Note: the numbers in curly brackets in this protocol refer to SPIRIT checklist item numbers. The order of the items has been modified to group similar items (see http://www.equator-network.org/reporting-guidelines/spirit-2013-statement-defining-standard-protocol-items-for-clinical-trials/).

## Introduction

### Background and rationale {6a}

Sepsis is one of the leading causes of neonatal morbidity and mortality [1]. Accurate and rapid diagnosis of early-onset neonatal sepsis (EOS), defined as sepsis onset within 72 h after birth, remains problematic mainly due to the non-specific signs and symptoms, and lack of reliable, rapid diagnostic tools. In the Netherlands, the national EOS guideline is used for the decision to start empirical antibiotics after birth. This guideline follows a risk-based approach including maternal and neonatal clinical risk factors [2]. Studies have shown that over 80% of preterm infants born below 32 weeks’ gestation are empirically started on antibiotics directly after birth, while the actual incidence of culture-proven EOS varies between 1 and 2% in this vulnerable population [3–5]. In other words, for every culture-proven EOS case, approximately 80 uninfected preterm infants are unnecessarily exposed to antibiotics directly after birth. Once started, antibiotics will be discontinued within 3 days in 70% of these infants, while in the remaining cases antibiotics are continued even in the absence of a culture-proven infection [3, 4]. Short-term complications of unnecessary antibiotic exposure in preterm infants are well described in the literature and include an increased risk for necrotising enterocolitis (NEC), late-onset sepsis (LOS), death, and antibiotic resistance [5–7]. A recently published national prospective observational study including 1259 preterm infants showed that those infants treated with antibiotics had a twofold increased risk for NEC, compared with the group of infants not treated with antibiotics [8]. Furthermore, a large Canadian observational study in preterm infants (*n *= 14,207) showed an association with a significantly increased risk for the composite outcome of severe intraventricular hemorrhage (IVH), LOS, NEC, retinopathy of prematurity (ROP), bronchopulmonary dysplasia (BPD), and death in infants exposed to antibiotics [9]. Potential long-term morbidities of early antibiotic use include a higher risk for asthma, allergy, and obesity due to aberrations in microbial colonization [10, 11].

Presepsin, also known as soluble CD14 subtype, is a novel biomarker showing rapid increase in blood after infection onset and having a high specificity for bacterial infections. Two recent meta-analyses showed a pooled sensitivity of 81–93% and specificity of 86–91% of presepsin for the diagnosis of EOS in neonates [12, 13]. Our prospective multicentre study provided a cut-off value for preterm infants that could significantly reduce antibiotic exposure without missing EOS cases, i.e. 645 pg/ml with 100% sensitivity and 54% specificity [14]. Before implementing presepsin in daily practice, a multicentre randomized controlled trial (RCT) is needed to confirm the hypothesis that adding a presepsin-guided decision to the Dutch EOS guideline is safe and effective in reducing antibiotic exposure.

For the patients assessed at low or high risk of EOS based on (lack of) risk factors and overt clinical symptoms, presepsin is preferably evaluated in an observational setting as diagnostic accuracy data in these groups are lacking. For both patient groups, these data could lead to improvement of the current Dutch EOS guideline. Currently, the sensitivity of the Dutch guideline for culture proven sepsis is approximately 50% in late preterm and term infants [15]. In high risk patients, the risk of withholding antibiotics for EOS is eliminated by means of the observational setting. This will ultimately contribute to a safe implementation of presepsin in all patients < 32 weeks of gestation.

### Objectives {7}

The objective of the randomized part of the study is to investigate whether adding a presepsin-guided decision to the Dutch EOS guideline safely reduces unnecessary empirical antibiotic exposure directly after birth in preterm infants born < 32 weeks of gestation categorized as moderate risk for EOS. Secondary, the objective of the observational study is to evaluate the diagnostic accuracy of presepsin in all preterm infants < 32 weeks of gestation.

### Trial design {8}

This is a multicentre, parallel groups, superiority and non-inferiority RCT with a concurrent observational study and is visualized in Fig. 1. The allocation ratio of the RCT is 1:1 in the intervention and comparator arm.

**Fig. 1 Fig1:**
[figure not shown]
Flowchart of the study design

## Methods: participants, interventions and outcomes

### Study setting {9}

The setting of the PRESAFE study will be in all nine Neonatal Intensive Care Units (NICU) in the Netherlands, and per September 25th 2024, the first centres have started including patients. The study is performed in collaboration with the Neonatology Network Netherlands (N3) organization (https://neonatology.eu/).

### Eligibility criteria {10}

All infants born at a gestational age of < 32 weeks are eligible for enrolment. After birth, as part of standard care, all infants will be classified into low, moderate, or high risk of EOS (Table 1) [2].

**Table 1 Tab1:** Classification of infants < 32 weeks in low, moderate or high risk of EOS

Low risk	Moderate risk	High risk—at least one of the criteria below
No indication to start empirical antibiotics according to the Dutch EOS guideline	Indication to start empirical antibiotics according to the Dutch EOS guideline, but no presence of high risk criteria (right column)	Suspected or proven EOS in other infants (in case of multiple births) or infants born to mothers with previous sibling with group B streptococcus disease/infection
		Suspected or confirmed diagnosis of maternal sepsis
		Unexplained respiratory insufficiency requiring invasive mechanical ventilation and FiO_2_ > 0.40 or non-invasive ventilation with FiO_2_ > 0.60 at time of randomization
		Ongoing hemodynamic instability requiring inotrope medication or more than 10 ml/kg fluid bolus at the timing of randomization
		Strong clinical concern for sepsis due to physical exam findings (i.e. minimal responsiveness, poor tone)

*AB *antibiotics, *BPD* bronchopulmonary dysplasia, *EOS *early-onset sepsis *GA *gestational age, *IVH* intraventricular hemorrhage, *LOS* late-onset sepsis, *NEC* necrotizing enterocolitis *PNA* postnatal age, *PSEP* presepsin, *PVL* periventricular leukomalacia, *ROP* retinopathy of prematurity, *UCB* umbilical cord blood

The moderate risk infants will be included in the randomized part of the study; the low and high risk infants are to be included in the concurrent observational part of the study. Exclusion criteria comprise absence (e.g. language barrier) or decline of informed consent.

### Who will take informed consent? {26a}

The study site coordinator or treating physician will inform parents and/or caregivers on the study verbally and obtain informed consent prenatally when applicable/possible. As the PRESAFE trial is a study that requires a time critical consent (randomization within 4 h after birth), we will use a two-stage consent pathway when there is no opportunity to approach women during the prenatal period. The two-stage consent pathway consists of a verbal agreement preferably before presepsin analysis and randomization, followed by written informed consent within 48 h after birth. If there is no opportunity to request verbal assent within 4 h after birth, a deferred consent procedure will be used with written consent obtained at the latest within 48 h after birth. In this situation, presepsin analysis, randomization, and possible treatment will be started before parents have been informed.

### Additional consent provisions for collection and use of participant data and biological specimens {26b}

Informed consent will also be obtained on the storage and possible future use of residual material from the collected blood.

## Interventions

### Explanation for the choice of comparators {6b}

N/A, see "Background and rationale {6a}".

### Intervention description {11a}

Infants at moderate risk of EOS will be randomly assigned (1:1 ratio) to the intervention or comparator arm. In the intervention arm, empirical antibiotics will only be started when the presepsin level is ≥ 645 pg/ml [14]. The result of the presepsin test will be communicated with the attending physicians as positive or negative without mentioning the exact level. Infants allocated to the comparator arm and those who will not be randomized will be treated according to standard care following the Dutch EOS guideline, with the treating physician and research team blinded to the presepsin test result.

### Criteria for discontinuing or modifying allocated interventions {11b}

In case of clinical deterioration of infants not receiving antibiotics allocated in the RCT intervention arm (based on a presepsin level under the threshold), the treating physician can decide to start antibiotic treatment after performing a sepsis evaluation (blood culture) if the infant fulfills at least one of the high risk criteria (Table 1). A second blood culture does not have to be performed when antibiotic treatment is started within 12 h after birth and thus after the first blood culture.

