### Relevant concomitant care permitted or prohibited during the trial {11d}

There is no relevant specific care permitted or prohibited during the trial.

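### Escape antibiotics need deterioration as well as a high-risk criterion, so maternal sepsis or EOS in a co-multiple first recognised after allocation opens no stated route to empirical treatment of a stable, presepsin-negative infant

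*Protocol article*

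**What the plan says.** In the Protocol article, Intervention description {11a} sets the default for the intervention arm: "empirical antibiotics will only be started when the presepsin level is" at or above 645 pg/ml. Criteria for discontinuing or modifying allocated interventions {11b} gives the one stated exception. It opens "In case of clinical deterioration of infants not receiving antibiotics allocated in the RCT intervention arm" and lets the treating physician start antibiotics after a sepsis evaluation "if the infant fulfills at least one of the high risk criteria (Table 1)". A repeat culture is waived if treatment begins in the first 12 h of life.

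Table 1, under Eligibility criteria {10}, lists five high-risk criteria, any one of which is enough. They include "Suspected or proven EOS in other infants (in case of multiple births)" and "Suspected or confirmed diagnosis of maternal sepsis". High-risk infants are not randomised and receive guideline care (Abstract, Methods).

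Background and rationale {6a} explains why. For low- and high-risk infants, "presepsin is preferably evaluated in an observational setting as diagnostic accuracy data in these groups are lacking". It adds: "In high risk patients, the risk of withholding antibiotics for EOS is eliminated by means of the observational setting". On other care, section {11d} says: "There is no relevant specific care permitted or prohibited during the trial".

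**The concern.** The same fact about the mother or the co-multiple has different consequences on either side of allocation. Before it, the fact alone takes the infant out of presepsin-guided withholding, and the stated reason is that the test's accuracy is not established in high-risk infants. After it, the fact alone opens nothing; the written rule waits for the infant to deteriorate.

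What is at stake is the safety of individual infants and consistency between sites. One clinician may treat a stable infant on the new information, while another may read {11a} and {11b} as a reason to hold back.

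**Working it through.** **1. The rule set out by timing.** Take an infant whose only high-risk criterion is maternal sepsis or EOS in a co-multiple.

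| First recognised | Infant's state | What the text provides |
|---|---|---|
| Before allocation | Stable or not | High risk, not randomised, guideline care |
| After allocation, presepsin-negative | Deteriorating | {11b} route open; the criterion is already met, so the ventilation, inotrope and fluid-bolus thresholds are not needed |
| After allocation, presepsin-negative | Stable | No stated route to empirical antibiotics |

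The gap is the last row.

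**2. Whether it can arise.** Randomisation takes place in the first 4 hours of life (consent section {26a}), so a sibling's culture result can be expected mostly after it. Siblings who both qualify share an arm (Sequence generation {16a}). A stable, presepsin-negative infant in the intervention arm can therefore have a co-twin found to have EOS after allocation.

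**3. How many infants.** Inputs from Sample size {14}: EOS incidence 1.4%, specificity 54%, 450 per arm.

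- Arm size, as a check: (1.645 + 0.842)² × 2 × 0.014 × 0.986 / 0.02² gives 427, and 427 / 0.95 gives 450. Both match the article.
- Uninfected, presepsin-negative, untreated infants: 450 × 0.986 × 0.54 = 239.6, about 240.
- Sibling route = arm size × share who are multiples × incidence in the sibling × probability that this infant tests negative. The multiples share is not given; I assume 20-35%, in pairs.
  - At 20%: 450 × 0.20 × 0.014 × 0.54 = 0.68 infants (0.15% of the arm).
  - At 35%: 450 × 0.35 × 0.014 × 0.54 = 1.19 infants (0.26%).
- Maternal route: no rate is given. Each 1% of the 240 untreated infants would be 2.4 infants. I claim no total.

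**4. What a negative test says.** The negative likelihood ratio is (1 − sensitivity) / specificity.

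- At the point estimate of sensitivity (100%) it is 0 / 0.54 = 0.
- At the lower confidence limit (78%) it is 0.22 / 0.54 = 0.41. Over the confidence limits for specificity it runs from 0.22 / 0.62 = 0.35 to 0.22 / 0.41 = 0.54.

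A negative result may exclude EOS or may only roughly halve the odds.

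**5. What a wider route would do to the superiority outcome.** Ten added starts, well above the sibling estimate, would be 10 / 450 = 2.2 percentage points, against the planned 30-point reduction.

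If a sibling's positive presepsin alone counted as suspected EOS, more infants would become treatable. With results independent within pairs:

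- 450 × 0.20 × 0.54 × 0.46 = 22.4 infants (5.0% of the arm)
- 450 × 0.35 × 0.54 × 0.46 = 39.1 infants (8.7%)

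The new wording should exclude that case.

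**The case against.** The strongest reply is that nothing here bars treatment. The restriction in {11a} concerns empirical antibiotics, which the Objectives tie to the period directly after birth. Section {11b} is permissive and describes one situation without saying that it is the only one. Section {11d} prohibits no specific care, and the SAE section {22} makes any later start reportable whatever its indication. This stands. A reader might infer that the protocol forbids treating such an infant; the text does not support that. It does not name the indication either, so the route is unstated, not closed.

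A reader might also infer that the infant goes unprotected until it deteriorates. That is too strong. Section {11b} refers to a first blood culture, the participant timeline lists a culture in both arms, and Outcomes {12} confines the lack of a standard culture to the low-risk group. Treating the infant's own positive culture would not be empirical. The safeguard is partial because it works only once that culture is positive.

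Requiring signs in the infant could be a deliberate choice in a trial of withholding on a negative test, and the rationale in {6a} concerns risk as assessed at classification. Two Table 1 criteria are worded for the time of randomisation, which suggests a classification table reused for escape, but that does not prove an oversight. The full protocol is not shown and may say more. The point survives because it concerns a rule that the article states, not a detail that it leaves out.

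**Conclusion.** The concern holds in a limited form. The only written escape route joins deterioration with a high-risk criterion, and this fits badly with two criteria that a stable infant can meet and that alone would have kept the infant out of the RCT. It is worth considering as a cheap improvement in individual safety; confidence is medium.

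The size is small: about 0.7 to 1.2 infants in the intervention arm by the sibling route. This rests on the assumed multiples share, on every sibling case becoming known only after allocation, on the 1.4% for all infants under 32 weeks holding at moderate risk, and on independence within pairs, which is doubtful for co-multiples. The maternal route cannot be sized.

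A reader might infer a threat to the non-inferiority or superiority conclusion. These numbers give no support for that, and the sample size is unaffected.

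**What to change.** Reword {11b} along these lines:

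> Within 72 h of birth, the treating physician can start antibiotics in an untreated intervention-arm infant after a sepsis evaluation (a blood culture, or the first culture if within 12 h of birth) if (a) the infant deteriorates and meets a high-risk criterion, or (b) maternal sepsis or EOS in a co-multiple is newly suspected on clinical grounds, or proven, after allocation, with or without deterioration. A positive presepsin result in a sibling does not by itself count as suspected EOS.

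The 72 h limit matches the definition of EOS in {6a} and stops limb (b) from running on indefinitely. The last sentence keeps the 22-39 presepsin-negative siblings, on the same assumptions, from becoming treatable through a sibling's test alone. The wording stays permissive: it supplies the missing route without obliging treatment.

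Recruitment is under way, so this is probably a substantial amendment to be notified to the ethics committee and site investigators (section {25}). Each added start is an SAE to be reported within 7 days (section {22}). If treatment lasts 3 days or less, it may count as unnecessary under the co-primary outcome. The resulting dilution is slight, 2.2 points even with ten added starts.

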### Strategies to improve adherence to interventions {11c}

N/A, see "Criteria for discontinuing or modifying allocated interventions {11b}".

### Relevant concomitant care permitted or prohibited during the trial {11d}

There is no relevant specific care permitted or prohibited during the trial.

### Provisions for post-trial care {30}

N/A, since there is no specific post-trial care other than regular follow-up at outpatient clinic.

### Outcomes {12}

#### Primary outcomes

The co-primary outcomes of the RCT part of the study are (1) the incidence of culture-proven EOS (non-inferiority) and (2) unnecessary antibiotics prescription started within the first 72 h after birth, i.e. ≤ 3 days of antibiotic administration (superiority). Antibiotic administration after birth is started to pre-emptively treat EOS. By adding a presepsin-guided decision to the Dutch EOS guideline for those infants qualifying for antibiotic treatment, the rate of antibiotic administration can presumably be reduced. However, it is imperative that this reduction in antibiotics in the RCT part of the study may not be outweighed by an increase in untreated (culture proven) EOS.

For the diagnostic accuracy of presepsin, we will include infants with moderate and high risk for EOS, directly after birth. The target condition is culture-proven sepsis. Accuracy measures that will be estimated are sensitivity, specificity, positive predictive value, negative predictive value, and area under the curve. The infants in the low-risk group will only be used for exploring the specificity of presepsin, as no standard blood culture will be drawn in this group.

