### Sample size {14}

Incidence of culture-proven EOS is assumed to be 1.4% based on the most recent and largest cohort with identical GA (< 32 weeks, *N* = 43,178) [4] and confirmed by screening 4 years admission data (2016–2019) of the NICU of Erasmus MC (Rotterdam, The Netherlands). With a plasma presepsin cutoff of 645 pg/ml, sensitivity is 100% (95% CI 78–100%) and specificity is 54% (95% CI 41–62%) for detecting EOS [14]. To balance the feasibility and the safety of the study, we have chosen a non-inferiority margin of 2% for the absolute between-RCT-arms difference in culture-proven EOS incidence (intervention–control) [24]. We deem this extra absolute risk acceptable in light of the incremental daily increased risk of adverse events with administration of antibiotics (NEC, LOS, death) [7]. Assuming there is no difference in culture-proven EOS between both study groups, a sample size of 427 is needed in both study groups (total *N* = 854), using a two-group, large-sample normal approximation test of proportions with 80% power and 1-sided 5% significance level. For the co-primary superiority outcome unnecessary antibiotics prescription < 72 h after birth, it is estimated that approximately 70% of all infants in the control group will discontinue antibiotics within 72 h (ref). Based on expert opinion, we consider an absolute reduction of 30% or more clinically relevant. Based on the aforementioned diagnostic accuracy of a presepsin cut-off level of 645 pg/ml, with a number of 427 in both study groups, we expect to detect a 30% reduction in the co-primary superiority outcome with a power of 99% and a 2-sided alpha of 0.05 (two-group Fisher’s-exact test). To allow for some unassessable cases (e.g. based on technical issues or withdrawn consent, estimated at 5%), a number of 450 will be included in both RCT-arms. The total study population is estimated to consist of 20% low risk (*N* = 244), 70% moderate risk (*N* = 900), and 10% high risk infants (*n* = 122).

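### The non-inferiority co-primary counts all culture-proven EOS, although the stated harm is untreated EOS, so infection already present in the first blood culture counts the same whether or not antibiotics are withheld

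*Protocol article*

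**What the plan says.** All references are to the protocol article.

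- **Primary outcomes:** "The co-primary outcomes of the RCT part of the study are (1) the incidence of culture-proven EOS (non-inferiority"; the second co-primary is unnecessary antibiotic prescription (superiority). The same paragraph says that the gain in antibiotic reduction "may not be outweighed by an increase in untreated (culture proven) EOS".
- **Sample size {14}:** "Incidence of culture-proven EOS is assumed to be 1.4% based on the most recent and largest cohort". On the margin: "we have chosen a non-inferiority margin of 2% for the absolute between-RCT-arms difference in culture-proven EOS incidence". The calculation begins "Assuming there is no difference in culture-proven EOS between both study groups" and uses "80% power and 1-sided 5% significance level", giving 427 per arm and 450 after a 5% allowance. The margin is justified by feasibility, safety and the risks of antibiotics; it is not set against the 1.4%.
- **Statistical methods {20a}:** non-inferiority is claimed if the upper one-sided 95% limit for the difference in culture-proven EOS is below 2%.
- **Intervention description {11a}:** in the intervention arm the presepsin result decides whether empirical antibiotics start. In the comparator arm presepsin is measured but the result is blinded.
- **Criteria for discontinuing {11b}:** a later antibiotic start within 12 h of birth is described as coming after the first blood culture.

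**The concern.** The harm that the protocol wants to exclude and the outcome that it tests differ by one word: untreated. An infant whose first culture is positive and whose presepsin is below 645 pg/ml is the case that the safety question is about. In the intervention arm antibiotics would be withheld from that infant at first; in the comparator arm a similar infant would be treated. Both add one to the co-primary count. For infection present at the first culture, the non-inferiority test therefore compares two groups that randomization has already made alike, and says little about whether presepsin found the infected infants.

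At stake is the wording of the main conclusion. The objective is a safe reduction in exposure, and Dissemination plans {31a} foresees use of the results in national and international guidelines. A non-inferiority result on total EOS could be read as evidence that withholding is safe when much of that result does not depend on how well the test performs.

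**Working it through.** **Inputs.** Sample size {14}: incidence 1.4% in both arms, true difference 0, margin 2%, one-sided alpha 5%, power 80%, 427 per arm, sensitivity 100% (95% CI 78–100%). Introduction: EOS is onset within 72 h. The various sensitivities below are assumptions used to show the range.

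**1. The plan's own figure.** n per arm = (1.645 + 0.842)² × 2 × 0.014 × 0.986 / 0.02² = 427, and 427 / 0.95 gives 450. Both reproduce; the arithmetic is not at fault.

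**2. The co-primary when infection is present at the first culture.** Expected cases per arm are 427 × 0.014 = 6.0. Suppose presepsin misses all six in the intervention arm. The comparison is still 6/427 against 6/427:

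- standard error = √(2 × 0.01405 × 0.98595 / 427) = 0.00806
- upper limit = 0 + 1.645 × 0.00806 = 1.33%, below 2%, so non-inferiority is claimed.

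With 1.4% in both arms, the chance of a claim is 80% by the normal approximation, 81% by enumerating the two binomials with a Wald limit, and 74% with a Newcombe limit. Sensitivity does not enter these calculations.

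**3. When the arms can separate.** If EOS arises or is detected after the first culture because antibiotics were withheld, the intervention count rises. At a true 2.8% against 1.4%, the chance of a claim falls to 15% (normal approximation) or 18% (enumeration, Wald). With 6 comparator cases, non-inferiority is claimed up to 8 intervention cases (upper limit 1.90%) and fails at 9 (2.18%). The endpoint does respond to this kind of harm.

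**4. Would untreated EOS with the same 2% margin be enough?** Take 0 untreated cases in the comparator arm and X ~ Binomial(427, 0.014 × (1 − sensitivity)) in the intervention arm. The 2% rule passes for X ≤ 4 with a Wald limit and X ≤ 3 with an exact (Clopper–Pearson) limit.

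| Sensitivity | True excess | P(pass), Wald | P(pass), exact |
|---|---|---|---|
| 78% | 0.31% | 99% | 96% |
| 50% | 0.70% | 82% | 65% |
| 0% | 1.40% | 29% | 15% |

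Even with every case missed, the true excess lies inside the margin. The margin would have to change along with the outcome.

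**5. What the same data can bound.** With zero cases in n infants, the exact one-sided 95% upper limit is 1 − 0.05^(1/n): 0.70% for 0/427 and 0.35% for 0/854. For 1/854 it is 0.55% and for 2/854 it is 0.74%.

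**6. Power of an illustrative bound of 0.7%.** It allows at most 1 case in 854. With X ~ Binomial(854, 0.014 × (1 − sensitivity)), P(X ≤ 1) is 88% at 95% sensitivity, 66% at 90% and 26% at 78%. The bound is strict.

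**The case against.** **Missed cases are already to be estimated.** The Primary outcomes section plans sensitivity and negative predictive value in moderate- and high-risk infants, with culture-proven sepsis as the target. The proposed count is the false-negative cell of that analysis, restricted to randomized infants. This stands, and it shows that the change is small. But the planned estimate has no decision rule, and nothing ties it to the safety claim of the RCT.

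**There are other safeguards.** A later antibiotic start in infants initially left untreated, and sepsis-related death, are reportable SAEs. The interim rule on mortality looks into the presepsin-low group. Meningitis, sepsis-related mortality and NEC, LOS or death are secondary outcomes. These make it unlikely that a poor test would go unnoticed. None sets a criterion for missed EOS, and the secondary outcomes are exploratory.

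**The endpoint is not inert.** A reader might infer that it cannot show anything about safety. The document does not support that: EOS runs to 72 h, a sepsis evaluation is foreseen on deterioration, and step 3 shows that a doubled incidence would usually fail. That every randomized infant has a first culture near birth is itself inferred, from section {11b}, the participant timeline, and the remark that only low-risk infants have no standard culture.

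**The margin exceeds the incidence.** A reader might take this as a free pass. It is not one on the endpoint in use, and the figures in step 4 belong to an outcome that the trial does not have. They matter only as a warning against changing the outcome and keeping 2%.

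**Moderate-risk incidence.** A reader might also infer that it lies below 1.4% because high-risk infants are excluded. Low-risk infants (20%) are excluded too, as against 10% high-risk, so the net direction cannot be told from the document.

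**Conclusion.** The concern holds in a limited form. The protocol names untreated culture-proven EOS as the harm and tests all culture-proven EOS. For infection already present in the first culture, the test is insensitive to whether presepsin detects it: about 81% chance of a non-inferiority claim at 1.4% in both arms and 427 per arm (74% with a Newcombe limit). EOS arising or detected later can still separate the arms, so the co-primary carries some safety information, but it does not by itself answer the question that the protocol poses.

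This rests on the 1.4% incidence, on a first culture taken before any later antibiotic start, and on that culture's result not depending on allocation. How many EOS cases would already be positive at the first culture is not given, so the share of the endpoint affected cannot be quantified.

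**What to change.** Keep the current co-primary and its sample size. By protocol amendment and in the SAP:

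- Prespecify as the key safety outcome of the RCT the number of culture-proven EOS cases within 72 h with presepsin below 645 pg/ml, among all randomized infants.
- Report it per arm and pooled, with an exact one-sided 95% upper limit. In the intervention arm these are infants from whom the presepsin result withheld antibiotics. In the comparator arm they are infants in whom it would have done so, which measures test accuracy and not harm from withholding. The report should keep the two apart.
- State that non-inferiority on total EOS incidence alone will not be reported as showing that withholding is safe.
- If a formal bound is wanted, the sponsor should choose it after a power check and set it below the 1.4% incidence. The 0.7% above is only an illustration.

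Tightening the margin on the present endpoint instead would be costly and would leave the mismatch in place: illustrative margins of 1.4%, 1.0% and 0.7% need 871, 1,707 and 3,484 per arm before the 5% allowance.

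The cost is wording and analysis: presepsin and cultures are already collected in both arms, and no treatment rule changes. The downside is that the safety claim becomes harder to obtain.
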